### **16.3 Spironolactone/Eplerenone Therapy visit (Baseline Visit)**

#### **(50mg) (post 2 week baseline visit)**

- Clinic BP will be measured similarly to home readings (using the same monitor) - in triplicate, after 5 minutes seated rest
- Updated medical history
- Concomitant medications
- Home blood pressure recordings for 4 days (as above)
- Electrolytes and renal function

#### **Spironolactone/Eplerenone (100mg) Visit week 4**

- Clinic BP will be measured similarly to home readings (using the same monitor) - in triplicate, after 5 minutes seated rest
- Updated medical history
- Concomitant medications
- Home blood pressure recordings for 4 days (as above)
- Electrolytes and renal function.
- Following up titration patient will have recheck of electrolytes and renal function either at clinic or as arranged with GP.

### **16.4 Post-surgical and non-surgical follow up schedule visits at 1, 3,6,12 and 24 months.**

Patients having adrenalectomy will be followed up at 1, 3, 6, 12 and 24 months. Final follow up visit will be up to two years following adrenalectomy. During these visits patients will have 3 blood pressures with heart rates measured in the clinic following 5 minutes seated rest. Home

blood pressures taken from diary will be recorded onto eCRF. Bloods will be taken for electrolytes, bicarbonate, creatinine, high troponin sensitivity test, brain natriuretic peptide (BNP), renin mass, renin activity, aldosterone and magnesium. Renin mass done at baseline and repeated post 6 months for adrenalectomy cohort and 6-9 months for aldosterone inhibitor medication cohort. (Please refer to schedule of events table). A serum HCG will be measured in child bearing potential females. Patients having a baseline CMR in this group will have a repeat at 6 -12 months following baseline CMR

For patients not requiring an adrenalectomy there will be at least one follow up visit at 9-12 following MDT. Patients having CMR in this group at baseline will have a repeat CMR at 6-12 months following MDT. Those recruited sufficiently early in the study, will have a second follow-up visit at about 2 years following MDT.

Patients from the adrenalectomy cohort will have a repeat or 24hr urine collection for metabolomics.

#### **16.5            Unscheduled Visits**

There will be provision in the eCRF for extra visits when considered necessary by the study team. This will not be considered a deviation of the protocol if these are not completed.

#### **16.6            Premature termination of therapy or follow up and replacement of withdrawals.**

Patients will be **withdrawn** from the study on safety grounds if any of the following occurs and at PI discretion:

- Illness requiring hospitalisation that is likely to preclude further study participation
- Sustained Hypertension  
Withdrawal will be up to PI discretion.
- Hypotension:  
If the patient has symptoms consistent with hypotension and systolic BP is <110mmHg or the change in BP from previous reading is >30mmHg, and in the opinion of the investigator there is no self-limiting reason for hypotension (e.g. episode of dehydration, climatic conditions) the patient will withdraw.....

All study withdrawals will be recorded in the study conclusion page of the eCRF, indicating the date and reason for withdrawal. The sample size calculation allows for a small (10%) withdrawal rate, but patients will where possible be replaced until 149 patients have completed the study.

NB: It will be expected that patients return their blood pressure monitors at the end of the study or at withdrawal.

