| Procedures for safety monitoring during trial                       | Serious adverse event reporting, symptom monitoring, BP monitoring and blood tests for creatinine and electrolytes.                                                                                                                                                                                                                                                                                                                                                                                                                                                                            |
| Criteria for withdrawal of patients on safety grounds               | New diagnosis which contra-indicates adrenalectomy.                                                                                                                                                                                                                                                                                                                                                                                                                                                                                                                                            |

|                                                  |                                                                                                                                                                               |
|--------------------------------------------------|-------------------------------------------------------------------------------------------------------------------------------------------------------------------------------|
| Adverse events and Serious Adverse events | Selected adverse and all serious adverse events will be recorded onto study database and reported to the sponsor Queen Mary University of London. Refer to SAE/A/E section 12 |
|--------------------------------------------------|-------------------------------------------------------------------------------------------------------------------------------------------------------------------------------|

---

|                                                 |                                                                                                                                             |

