### 10.3 Withdrawal Criteria

Unwillingness or inability to undergo both PET CT and AVS or at the PI discretion.

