## **20.0 Study Outcomes**

### **20.1 Primary Outcome(s)**

1. Change in ARR from baseline to 6 months after surgery, or 9-12 months after MDT in patients not proceeding to surgery. (For patients whose surgery takes place less than six months prior to overall study-end, data will be used from the 3 month post-op visit, or the six-month visit will be brought forward. This qualification applies to all other reference to the six-month visit and data in this protocol.)
2. Change in SBP (mean of at least 12 measurements from 3 days home monitoring), from baseline to 6 months after treatment, or 9-12 months after MDT in patients not proceeding to surgery

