## **1.8. OUTCOMES**

Outcomes for statistical analysis will be assessed at 6 months after surgery, or 9-12 months after MDT decision, in those who do not undergo surgery. These time points are considered equivalent, occurring at approximately the same time since baseline. Where follow-up data is not available at this time point, data from a later visit (up to 12 months) will be used; if this is not available, an earlier visit (closest available) will be used.

Outcomes for statistical analysis will be referred to as collected “at 6 months” throughout this SAP.

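### Protocol 16.6 takes patients out of the study, not just off a treatment, for a blood pressure event, and nothing keeps them in 6-month outcome follow-up

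*Combined protocol and SAP*

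**What the plan says.** Protocol 16.6 withdraws patients "from the study on safety grounds if any of the following occurs and at PI discretion". The listed events are hospitalisation likely to prevent further participation, sustained hypertension (no threshold, left to the PI), and hypotension. The hypotension rule reads "If the patient has symptoms consistent with hypotension and systolic BP is <110mmHg or the change in BP from previous reading is >30mmHg", and applies when the investigator sees no self-limiting reason. Its consequence is that the patient leaves the study; no therapy-only route is given, although the section title mentions therapy as well as follow-up.

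The date and reason go on the study conclusion page of the eCRF. It is expected that "patients return their blood pressure monitors at the end of the study or at withdrawal". On numbers, "patients will where possible be replaced until 149 patients have completed the study".

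The other withdrawal lists contain no blood pressure trigger. The synopsis gives "New diagnosis which contra-indicates adrenalectomy"; section 10.3 gives "Unwillingness or inability to undergo both PET CT and AVS or at the PI discretion".

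The SAP's full analysis set is everyone enrolled who had both tests, and each primary outcome is analysed in those of them who have surgery (SAP 2 and 2.3.1). For a missing 6-month value, SAP 1.8 first takes a later visit, up to 12 months; then, "if this is not available, an earlier visit (closest available) will be used". Protocol 20.1 allows a narrower substitution: "For patients whose surgery takes place less than six months prior to overall study-end, data will be used from the 3 month post-op visit". Its alternative is to hold the 6-month assessment early.

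**The concern.** Blood pressure is both a trigger for leaving the study and part of the outcome. Adrenalectomy is meant to lower it, and the synopsis expects antihypertensives to be tailored down afterwards. A patient who becomes hypotensive while still on drugs may be on the way to complete clinical success, which under SAP 1.9 requires taking none. If that patient is withdrawn, the score can be fixed at an earlier visit, while drugs were still being taken. Replacement restores a head count but does not recover the missing value.

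The exposure differs by outcome:

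- **Complete clinical success** (fourth in the SAP hierarchy) and the protocol's SBP change are the most exposed.
- **At least partial clinical success** is less exposed. A hypotensive patient still on drugs would usually qualify already, through normalised BP with a drug dose under 150% of baseline.
- **The biochemical outcomes** are affected mainly through the earlier date, since ARR and potassium are also measured at 4 weeks and 3 months after surgery.

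The only sensitivity analysis of the primary outcomes (SAP 2.3.6) excludes AVS technical failures, so it does not examine this.

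**Working it through.** **1. The protocol's completer figure.** 165 recruits × (1 − 0.10) = 148.5, rounded up to 149. This matches 16.6. It is a count of completers and says nothing about outcomes lost to withdrawal.

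**2. Does any text keep a withdrawn patient in outcome follow-up?**

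| Place | What it does |
|---|---|
| Protocol 9.2 | Puts patients with both tests in the ITT analysis |
| Protocol 14.3 | Retains data already stored after consent withdrawal |
| Protocol 16.5 | Provides for extra visits |
| Protocol 16.7 | Leaves further care to the clinical physician |
| Protocol 17.0 | Follows SAEs to resolution |
| SAP 1.8, 1.10.2 | Substitutes other visits or carries values forward |

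None asks a site to collect the 6-month (or 9-12 month) outcome after a 16.6 withdrawal. SAP 1.8 also has no floor: read literally, the closest earlier visit may precede surgery.

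**3. Size of one wrong score.** The documents give no rate of BP-triggered withdrawal, so only a per-patient effect can be calculated. Inputs are the 70 operated patients of protocol 12.1 and the planning table of protocol 33.0 (repeated in SAP 1.5). The table describes ARR normalisation, the only mix given. Accuracy follows SAP 2.3.1: a test is correct if it indicated unilateral disease and cure followed, or did not and cure did not follow.

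Per 100 recruits:

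- PET only indicated surgery: C+D+G+H = 1+10+1+9 = 21, of whom D+H = 19 cured and 2 not.
- AVS only: I+J = 0.5+3.5 = 4, of whom 3.5 cured and 0.5 not.
- Both unilateral: K+L+M+O+P+Q = 31, of whom L+O+Q = 29.5 cured and 1.5 not.
- Operated: 21+4+31 = 56. Single-test share: 25/56 = 45%.

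Scaled to 70 operated and rounded:

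- only PET correct: (19+0.5)×70/56 = 24.4, taken as 24
- only AVS correct: (2+3.5)×70/56 = 6.9, taken as 7
- both correct: 29.5×70/56 = 36.9, taken as 37
- both wrong: 1.5×70/56 = 1.9, taken as 2

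One wrong cure score moves the success rate by 1/70 = 1.4 points. In a single-test patient it also swaps which test was right, so the accuracy difference moves by 2/70 = 2.9 points, in either direction. Where both tests indicated surgery, the difference moves by 0.

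**4. Errors needed to change a conclusion, for scale only.** Each net error against PET takes one patient from the first group and adds one to the second. The intervals are Newcombe paired 95% intervals; p is from the exact McNemar test.

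| Net errors against PET | PET only / AVS only correct | Difference (95% CI) | p |
|---|---|---|---|
| 0 | 24 / 7 | 24.3% (9.2 to 38.0) | 0.003 |
| 2 | 22 / 9 | 18.6% (3.2 to 32.9) | 0.029 |
| 3 | 21 / 10 | 15.7% (0.2 to 30.2) | 0.071 |
| 7 | 17 / 14 | 4.3% (−11.2 to 19.5) | 0.72 |
| 9 | 15 / 16 | −1.4% (−16.8 to 14.0) | – |
| 10 | 14 / 17 | −4.3% (−19.5 to 11.2) | – |

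Superiority needs p<0.05 and a lower limit above 0, so it survives 2 net errors and fails at 3. Non-inferiority at −17% survives 9 and fails at 10.

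**The case against.** The path to a wrong primary outcome is narrow. The hypotension rule needs symptoms, a BP criterion, no self-limiting cause and the PI's agreement; sustained hypertension is wholly discretionary. A PI can reduce drugs without withdrawing anyone. The forced spironolactone/eplerenone titration precedes surgery, and a patient withdrawn then and never operated on is outside the primary analysis. A patient withdrawn for sustained hypertension would often score as a BP failure at either visit. The outcome most exposed is primary only if three earlier analyses succeed, and the thresholds above come from a different outcome's mix. Even if the whole 10% allowance (7 of 70) were single-test patients mis-scored against PET, the lower limit would be −11.2%, inside the margin. All of this stands, and it keeps the point minor.

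Two further arguments concern the fallback. SAP section 3 defers missing-data rules to a separate validation plan, which is not available here and could contain a floor. A pre-surgical substitute is also a strained reading, since the criteria are defined after adrenalectomy and the week 2 and week 4 lists include no renin or aldosterone. The second argument does limit the gap largely to blood pressure outcomes in operated patients with no post-operative visit. Neither changes the wording of SAP 1.8, and no data rule can recover a visit that was never held.

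The plan also covers part of the problem. Withdrawal reasons are recorded, visit completion is reported (SAP 2.1), and summaries are shown with and without imputation where values are carried forward (SAP 1.10.2). These make the loss visible but do not prevent it.

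**Conclusion.** The concern holds, as a minor one. Followed as written, 16.6 can remove a patient before 6 months because of blood pressure, and SAP 1.8 then scores a BP-based outcome at an earlier date. This is a rule that can bias, not merely an omitted detail.

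The number affected is unknown and possibly zero. The direction, including for PET against AVS, cannot be determined from the documents. With 70 operated patients, each wrong score is worth 1.4 points on the success rate, and 2.9 or 0 points on the accuracy difference. The thresholds of 3 net errors for superiority and 10 for non-inferiority assume the planning mix for ARR normalisation. No mix is given for complete clinical success, so no effect on its conclusion is claimed.

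**What to change.** - **Protocol 16.6:** separate stopping or changing a treatment from leaving the study. The clinical criteria stay as they are, applied by the clinical team. Patients who meet a blood pressure criterion keep the monitor, attend the scheduled 6-month or 9-12 month visit unless they withdraw consent, and are not replaced for blood pressure reasons.
- **SAP 1.8:** limit the earlier-visit fallback to post-treatment visits, which for operated patients means post-surgical visits. Report how many primary outcomes come from an earlier visit after a 16.6 withdrawal.

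The cost is minor wording in two places, a memo to sites, and a few visits that are already scheduled. If follow-up has finished, the SAP change and the count can still be made before the final analysis.

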### **16.7 Plan of Further Treatment**

Patients will be managed by their clinical physician.

## **17.0 Adverse events (AE/SAE)**

Definition of Adverse Event

adverse event (ae) – any unfavourable and unintended sign, symptom or disease temporally associated with participation in the research project.

Definition of Serious Adverse Event

Serious adverse event (SAE) - an untoward occurrence that:

- a. results in death
- b. is life threatening
- c. requires hospitalisation or prolongation of existing hospitalisation and results in persistent or significant disability or incapacity
- e. consists of a congenital anomaly or birth defect
- f. is otherwise considered medically significant by the investigator

Recording and reporting Serious Adverse events

AEs will be identified by observation and /or enquiry at study visits. AEs that do not meet criteria for seriousness will be recorded in the medical notes only. Details of SAEs will be reported to the pharmacovigilance office at Queen Mary University of London (sponsor) using the QMUL Non CTIMP SAE form. Once aware of a SAE, scan and email/fax signed SAE form to the Research Governance & GCP Manager: **[name] making sure subject number and site are added to form or email [[contact]](mailto:[contact])** copying in MATCH trial coordinator via email.

Please send all unexpected and related SAEs to the QMUL sponsor immediately. SAEs will be followed until resolution. The relationship with the study procedures will be assessed for all SAEs. All 'study related' SAEs will be forwarded to the CI and PI for assessment of the expectedness. All 'possibly' or 'definitely' related, unexpected SAEs will be reported to the REC on annual report.

All SAEs related to the study will be reported by the principal investigator (or designee) to sponsor as soon as reasonably practicable and in any event within 24 hours of first becoming aware of the event. Any follow up information should also be reported.

The SAE will need to be recorded onto MATCH eCRF in SAE section also for CI/PI review. All SAEs will be reviewed at TSC.

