## **2.4. SAFETY OUTCOMES**

### **2.4.1. SERIOUS ADVERSE EVENTS**

The characteristics of all serious adverse events (SAEs) recorded in the study will be summarised, including severity, relationship to study procedures, outcome, and duration. The number and percentage of participants experiencing at least one SAE will be reported as a whole and by MedDRA system organ class and preferred term. Summaries will be provided as a whole and in relation to whether the participant underwent surgery. For those who underwent surgery, summaries will be provided according to whether the onset date was prior to or after the date of surgery.

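### SAE item c in protocol 17.0 joins hospitalisation and disability with *and* (item d is missing), so neither alone makes an event serious unless another item applies

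*Combined protocol and SAP*

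**What the plan says.** Protocol 17.0 defines an SAE by a lettered list. Items a and b are death and an event that "is life threatening". Item c is an event that "requires hospitalisation or prolongation of existing hospitalisation and results in persistent or significant disability or incapacity". There is no item d. The next entry is "e. consists of a congenital anomaly or birth defect", and the last, item f, is an event that "is otherwise considered medically significant by the investigator".

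The same section says where events go. Of other adverse events it says "AEs that do not meet criteria for seriousness will be recorded in the medical notes only". SAEs go to the sponsor on its SAE form, and all are reviewed by the Trial Steering Committee (TSC). On data entry: "The SAE will need to be recorded onto MATCH eCRF in SAE section also for CI/PI review".

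The synopsis (protocol 3.0, row on adverse events) says something different: "Selected adverse and all serious adverse events will be recorded onto study database". It does not say which adverse events are selected. It refers the reader to section 12, which in this protocol concerns sites and investigators.

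Protocol 24.2 plans no data monitoring and ethics committee (DMEC) and has SAEs reported to the TSC. SAP 2.4 contains one subsection, 2.4.1, which begins "The characteristics of all serious adverse events (SAEs) recorded in the study will be summarised".

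**The concern.** Hospitalisation and disability read like two separate criteria run together. The letter d is missing exactly where the second would begin, and a conjunction stands in its place.

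The definition is operative. The SAE label decides whether an event produces a sponsor form, an entry in the eCRF SAE section, TSC review and a row in the SAP's event tables. For related and unexpected events it also decides whether the ethics committee is told (protocol 17.1). With no DMEC, the TSC's view of harm depends largely on that label.

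The study contains procedures after which an admission or a longer stay without permanent disability is a plausible form of harm. Protocol 6.2 names bleeding and adrenal infarction as rare or very rare risks of adrenal vein sampling. Protocol 11.0 force-titrates spironolactone/eplerenone subject to blood pressure and potassium conditions. Adrenalectomy is expected in 70 patients (protocol 23.0) or 90 (synopsis). An admission of this kind is what item c, read literally, leaves out.

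**Working it through.** No arithmetic applies. The check is a logical reading of item c, followed by tracing where each kind of event is recorded.

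**Step 1: how item c parses.** The two verbs (requires, results in) are joined by *and*. The *or* sits inside the object of the first verb. The grammatical reading is therefore

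c = (hospitalisation OR prolongation) AND (disability OR incapacity).

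Write H for the first bracket and D for the second. As written, c = H AND D. Split into two items, c or d = H OR D.

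| Event | c as written | c or d if split |
|---|---|---|
| H and D | met | met |
| H without D | not met | met |
| D without H | not met | met |
| neither | not met | not met |

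The two readings differ in two of the four rows: admission or prolonged stay without disability, and disability without admission.

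**Step 2: whether another item rescues those two rows.**

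- Item a (death), item b (life-threatening) and item e (congenital anomaly) do so only for events of those specific kinds.
- Item f does so if the investigator judges the event medically significant.

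An ordinary admission that is neither fatal nor life-threatening therefore depends on item f. This replaces an observable trigger (was the patient admitted?) with a judgement made at approximately three sites (synopsis) or three to six (protocol 12.1).

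**Step 3: where an event goes if it is not classed as serious.**

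| Destination | SAE | Not an SAE |
|---|---|---|
| Sponsor SAE form (17.0) | yes | no |
| eCRF SAE section (17.0) | yes | no |
| TSC review (17.0, 24.2) | yes | not required |
| Event summary (SAP 2.4.1) | yes | no |
| Medical notes (17.0) | – | yes, and there only |
| Study database (synopsis) | yes | if selected; selection undefined |

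The last two rows conflict for non-serious events.

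**Step 4: partial routes to the database.** Protocol 16.6 puts withdrawals on the study conclusion page of the eCRF with date and reason, including withdrawal for a hospitalised illness likely to prevent further participation. Protocol 16.5 provides eCRF space for unscheduled visits. The first catches an admission only if it leads to withdrawal, and the second only if an extra visit is made and entered. Neither generates an SAE report.

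**Step 5: size.** The documents give no rate of admission, prolonged stay or disability, so the number of events affected cannot be calculated.

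**The case against.** The strongest reply is that this is clerical and may be harmless. The missing letter suggests two items ran together, and experienced sites may already treat any admission as serious. The sponsor's SAE form and the eCRF SAE page are not in the documents. If they list the criteria separately, practice could be sound. A letter lost in reading the PDF also cannot be ruled out. Much of this stands: the practical effect depends on forms that cannot be seen, and no under-reporting is shown. But a lost letter would not by itself account for the *and*, and the protocol text is the definition that sites are given.

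Four stronger readings are tempting, and the documents do not support them:

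- **That the SAE definition as a whole requires hospitalisation and disability together.** Only item c does. Items a, b, e and f are separate routes.
- **That most admissions would be missed, or that these would be the largest class of SAEs.** No figure supports either. The protocol describes bleeding after adrenal vein sampling as rare (6.2) and reports more than 300 previous metomidate scans without serious adverse events (24.2).
- **That missed admissions would never reach the database.** The synopsis puts selected adverse events there, and protocol 16.5 and 16.6 offer partial routes.
- **That SAEs are the SAP's only safety outcome.** SAP 1.2.3 also names symptoms, blood pressure and renal function. Potassium, creatinine and eGFR are summarised at weeks 2 and 4 (SAP 2.2.5 and 2.2.6) and at later visits (2.2.9 to 2.2.13). High potassium at a scheduled visit would therefore appear in those summaries, though an admission between visits might not. SAEs are the only events summarised under SAP 2.4.

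**Conclusion.** Wrong as written: a drafting error in an operative definition, not a design choice. Read literally, item c excludes an admission or prolonged stay without disability, and disability without admission. Either is serious only through another item, in practice mainly item f. Some admissions could therefore be absent from sponsor SAE reports, the eCRF SAE section, TSC review and the SAP 2.4 event summary.

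The number affected cannot be determined. The conclusion assumes that sites apply the protocol text as it stands. If the SAE form and eCRF already list the two criteria separately, the practical effect could be small, but the text would still need correcting. The disagreement between the synopsis and section 17.0 over non-serious events holds on either assumption. The point does not touch the efficacy analyses.

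**What to change.** 1. Split item c of protocol 17.0 at the *and*. Item c keeps the hospitalisation-or-prolongation wording alone. A new item d carries the disability-or-incapacity wording alone. Each is sufficient by itself.
2. Check that the sponsor's SAE form and the eCRF SAE section use the same list.
3. Reconcile the synopsis with protocol 17.0: either state which non-serious adverse events go on the study database, or state that none do. Correct the synopsis cross-reference, which should point to section 17.

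The cost is a short protocol amendment, a check of two forms and slightly more SAE forms to complete. No endpoint, sample size or treatment rule changes. If sites already report every admission, the edit only aligns the text with practice.
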